## Abstract

**Introduction:**

The liberal use of blood cultures in emergency departments (EDs) leads to low yields and high numbers of false-positive results. False-positive, contaminated cultures are associated with prolonged hospital stays, increased antibiotic usage and even higher hospital mortality rates. This trial aims to investigate whether a recently developed and validated machine learning model for predicting blood culture outcomes can safely and effectively guide clinicians in withholding unnecessary blood culture analysis.

**Methods and analysis:**

A randomised controlled, non-inferiority trial comparing current practice with a machine learning-guided approach. The primary objective is to determine whether the machine learning based approach is non-inferior to standard practice based on 30-day mortality. Secondary outcomes include hospital length-of stay and hospital admission rates. Other outcomes include model performance and antibiotic usage. Participants will be recruited in the EDs of multiple hospitals in the Netherlands. A total of 7584 participants will be included.

**Ethics and dissemination:**

Possible participants will receive verbal information and a paper information brochure regarding the trial. They will be given at least 1 hour consideration time before providing informed consent. Research results will be published in peer-reviewed journals. This study has been approved by the Amsterdam University Medical Centers’ local medical ethics review committee (No 22.0567). The study will be conducted in concordance with the principles of the Declaration of Helsinki and in accordance with the Medical Research Involving Human Subjects Act, General Data Privacy Regulation and Medical Device Regulation.

**Trial registration number:**

NCT06163781.

STRENGTHS AND LIMITATIONS OF THIS STUDYPioneering the use of machine learning in a randomised controlled trial to predict blood culture outcomes.Conducting a comparative analysis against current clinical practices.Assessing patient-centred outcomes and performing an economic evaluation.May restrict future applications due to the exclusion of immunocompromised patients.

## Introduction

Over 20% of adult emergency department (ED) visits occur due to infections.^1^ Often, physicians will request blood cultures in these patients due to fear of a bloodstream infection (BSI).^2^ Because of the liberal use of blood cultures, the yield tends to be low. Depending on the setting, only about 1%–15% of blood cultures grow pathogens, of which 30%–55% turn out to be false-positive, contaminated results.^3–5^ Those contaminated cultures are associated with prolonged hospital stays, unnecessary use of antibiotics and even hospital mortality.^3 6 7^ To optimise blood culture use, it is crucial to better target which patients would benefit from blood culture analysis.^8^

A machine learning model based on extreme gradient-boosting (XG Boost) that can predict the outcome of blood cultures in the ED has been developed to address this clinical dilemma, aiming to reduce unnecessary tests in low-risk patients, and help avoid the harms associated with false-positive results due to blood culture contamination.^9 10^ The performance of the model has been internally and externally validated in various settings, including a real-time background evaluation in the Amsterdam University Medical Centers (Amsterdam UMC, locations VUmc and AMC) Electronic health record (EHR) system, where it maintained an area under the operating curve of 0.76 and showed a potential reduction of approximately 30% blood cultures in the future.^9 10^ Additionally, the model has shown a consistent performance over time despite changes in clinical practice and patient characteristics.^11^

The aim of this study is to investigate the safety and potential clinical benefits of using the blood culture prediction tool as decision support in reducing unnecessary blood cultures and thereby the negative side effects of false-positive results for patients. This will be the first randomised controlled trial testing such a machine learning prediction tool in clinical practice.

## Methods and analysis

This study protocol adheres to the Standard Protocol Items: Recommendations for Interventional Trials statement.

### Model development and validation

This segment features a summary of the model development, more detailed descriptions have been published previously.^9 10^ For the development of the model data from the VUmc was split into a training (80%) and a test set (20%), stratified by blood culture outcomes. Missing data were imputed by medians. The model was trained on the training set and subsequently validated in the VUmc test set, and three other hospital datasets (AmsterdamUMC location AMC, Zaans Medisch Centrum (ZMC, Zaandam, The Netherlands) and Beth Israel Deaconess Medical Center (BIDMC, Boston, Massachusetts, USA)). These hospitals differ in size and population, comprising two tertiary teaching hospitals and one secondary care hospital in the Netherlands, along with one hospital dataset from the USA. Part of the data was gathered during the COVID-19 pandemic, but this did not affect its performance. The model contains 49 variables, namely age, sex, 6 vital sign measurements and 18 laboratory tests. Additionally, indicator variables of the laboratory tests were included. Figure 1 shows the 20 most important variables. The area under the receiver operating characteristic (AUROC) curves in the various validation cohorts ranged between 0.75 and 0.81. A prospective validation was also performed, integrating the model into the EHR of VUmc, showing an AUROC of 0.76. With the threshold for blood culture analysis set at 5%, analyses could be avoided at approximately 30%.

**Figure 1 F1:**
[figure not shown]
SHAP values for model variables. This figure depicts SHAP (SHapley Additive exPlanation) values, illustrating the individual contributions of each variable to the model’s prediction. In the left panel (blue bars), we see the average impact of the 20 most important features on the prediction. Meanwhile, the right panel not only shows the feature’s contribution but also its direction. Contributions to the left of 0 on the x-axis correspond to negative predictions for blood cultures, while those to the right correspond with positive predictions. Additionally, the colour indicates the predictor’s actual value, with blue indicating low values and red indicating high values.

### Study design

This study will be a multicentre randomised controlled non-inferiority trial. Participants will be randomised into an intervention and control arm. In the intervention group, the blood culture prediction model is used to predict the probability of a positive blood culture in the patient. The model will start predicting when sufficient variables are available in the EHR. A new prediction will be made every 20 min until 3 hours have passed since check—in of the patient in the ED. The predictions made by the model will be shown to the physician after randomisation in a dashboard integrated into the EHRs. The blood culture analysis will be cancelled if the probability of a positive culture is less than 5%. This will be done manually by the study team. If the probability is over or equal to 5%, the blood culture will be analysed as per standard practice. In the control group, all patients will have their blood cultures analysed. The study design is summarised in figures 2 and 3. Patients will be randomised within the EHR system, to ensure that physicians cannot be influenced in their treatment decisions by seeing the score before the patient is included. The first patient was included in February 2024. Follow-up of the last patients is expected in February 2027.

**Figure 2 F2:**
[figure not shown]
Consolidated Standards of Reporting Trials flow chart.

**Figure 3 F3:**
[figure not shown]
Study design flow chart.

### Population

All adult patients (aged 18 years or older) presenting to the EDs of multiple hospitals in the Netherlands, and in whom blood cultures are ordered during ED stay will be assessed for eligibility. This process is automated within the EHR. The treating physician determines whether there is an indication for performing blood cultures according to the current local standards, after which both the patient and study team are informed about possible study recruitment. Inclusion and exclusion criteria are summarised in table 1. Some patients will be excluded due to the higher possibility of BSIs with a pathogen generally considered a contaminant (eg, a central line in situ) or because of the possibility of severe clinical implications of omitting blood cultures (eg, severe neutropenia). Since the study’s goal is to reduce unnecessary testing, patients for whom blood culture analysis is deemed imperative are excluded (eg, patients with a suspected diagnosis of endocarditis, spondylodiscitis or infected prosthetic material). Furthermore, patients unable to give informed consent and pregnant or breastfeeding patients will be excluded, due to them being considered high-risk groups by the ethics review board. Therefore, the review board did not give permission to include these groups.

**Table 1 T1:** Overview of inclusion and exclusion criteria

Inclusion criteria	Age ≥18 years
	Willing and able to give informed consent to participate
	Have a clinical indication for blood culture analysis (according to the treating physician)
	Have sufficient data recorded (laboratory results and vital sign measurements) for a prediction to be made*
Exclusion criteria	Patients with a central venous catheter or peripherally inserted central catheter in situ
	Neutrophil count <0.5×10^9^ /L
	Candidemia or *Staphylococcus aureus* bacteremia in the past 3 months
	Suspected endocarditis, spondylodiscitis or infected prosthetic material
	Pregnant or breastfeeding patients
	Inability to give informed consent

*Predictions can only be made when at least 20% of the needed parameters are available for a patient, which is the case in approximately 80% of all patients who undergo blood culture analyses in the emergency department.

### Sample size calculation

An analysis of 5907 unique ED visits with blood culture sampling in Amsterdam UMC showed a 30-day mortality rate of 7.6%, a hospital admission rate of 67.4% and an average length of stay in the hospital of 6.7 days. Based on these numbers, the sample sizes with a relative non-inferiority margin of 1.25 for the rates and 1 day for the length of stay were calculated. The sample sizes were calculated by a statistician based on a one-sided alpha of 5% and a target power of at least 80%. For 30-day mortality, the calculated sample size was 6066 (3033 per arm) to test non-inferiority. After inflation for a dropout rate of 20%, the final sample size is 7584 (3792 per arm). For the secondary outcomes, described in table 2, fewer participants were needed for adequate power.

**Table 2 T2:** Overview of outcome measures

Primary outcome	30-day all-cause mortality
Key secondary outcomes	In-hospital mortality
	Hospital admission rates
	Hospital length-of-stay
Other outcome measures	
Patient-related outcomes	90-day mortality
	30-day readmission rates
	Emergency department length-of-stay in hours
Diagnostics related outcomes	Percentage of blood cultures avoided in the intervention group
	Number of blood cultures on each day of hospital stay (in admitted patients)
	Percentage of positive blood cultures in each group
	Total number of laboratory and microbiology tests in the ED
	Total number of laboratory and microbiology tests on each day of hospital stay (in admitted patients)
Therapy-related outcomes	Percentage of patients receiving antibiotics in the ED
	Duration of antibiotic therapy
	Types of antibiotics given in the ED
Model-related outcomes	Model performance (AUC) during the trial
	Model performance in subgroups: Immunocompromised patients (triple immunosuppressive therapy) Patients who had transplants

AUC, area under the operating curve; ED, emergency department.

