### Statistical analysis

We will carry out a per-protocol analysis. The primary outcome, the 30-day mortality rate, will be compared between the groups using a non-inferiority test for the ratio of two proportions. This will be a one-sided test with a significance level of 0.05. Additionally, we will do a multivariable analysis of the primary and key secondary outcomes to adjust for potential effect of age, Charlson Comorbidity Index, use of immunosuppressive medication, Modified Early Warning Score and resuscitation status. Similar tests will be performed for in-hospital mortality rate and the hospital admission rate. The hospital length-of-stay will be analysed as a continuous variable and a non-inferiority test for the differences between the two means will be used. The test statistic to be used is a one-sided T-test with a significance level of 0.05. The model-related outcomes will be assessed using an area under the curve and calibration plots. Baseline characteristics will be presented using descriptive statistics, without statistical testing for differences, since this is a randomised trial.

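### The 1.25 ratio margin, applied to a 67.4% admission rate, tolerates a rise of 16.85 percentage points, so non-inferiority on hospital admission would say little about realistic increases

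*Protocol article*

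**What the plan says.** The section Sample size calculation takes its reference figures from 5907 emergency visits with blood culture sampling: 30-day mortality of 7.6%, and "a hospital admission rate of 67.4% and an average length of stay in the hospital of 6.7 days". It then uses a "relative non-inferiority margin of 1.25 for the rates and 1 day for the length of stay", with a "one-sided alpha of 5% and a target power of at least 80" per cent. For mortality, "the calculated sample size was 6066 (3033 per arm) to test non-inferiority"; after 20% dropout this becomes 7584 in total. The section adds that the secondary outcomes required smaller numbers.

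Table 2 lists hospital admission among the key secondary outcomes. The section Statistical analysis specifies a one-sided 0.05 non-inferiority test on the ratio of two proportions for mortality and continues: "Similar tests will be performed for in-hospital mortality rate and the hospital admission rate". The article gives no separate margin for admission and no reason specific to admission.

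**The concern.** A ratio margin means different things at different base rates. A ratio of 1.25 on a 7.6% event allows a small absolute rise. On an event that already occurs in two thirds of patients, the same ratio uses up a large part of all the room there is for worsening. The admission rate is nearly nine times the mortality rate (67.4/7.6 = 8.9), so the absolute allowance is also nearly nine times as large.

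What is at stake is a key secondary claim. The trial aims to show safety and clinical benefit and plans a cost-effectiveness analysis. A statement that the tool is non-inferior on admissions would be read as reassurance that admissions do not rise materially. If the rule passes almost surely when there are 10 extra admissions per 100 patients, that reading would be wrong.

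**Working it through.** **Inputs.** All are from the protocol article: admission 67.4%, mortality 7.6%, ratio margin 1.25, one-sided alpha 0.05, power 80%, 3033 evaluable per arm, 1:1 allocation. About 30% of culture analyses are expected to be avoided (Model development and validation). It is assumed that a higher admission rate is the unfavourable direction, as the non-inferiority test implies, and that the control rate equals the reference rate.

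**Reproducing the plan's own figure.** For 7.6% in both arms, the score test for a ratio of proportions (Farrington–Manning, variance under the null from the restricted maximum likelihood estimates) gives 3032.2, so 3033 per arm, as stated. The simpler log risk ratio formula, n = (1.645 + 0.842)² × 2 × (0.924/0.076) / (ln 1.25)², gives about 3020. Dropout: 3033/0.8 = 3792 per arm, 7584 in total. Reading the margin as a risk ratio is therefore right, and the primary sample size is sound.

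**The margin on the absolute scale.**
- Mortality: 0.076 × 0.25 = 1.9 points.
- Admission: 0.674 × 1.25 = 0.8425, so 84.25 − 67.4 = 16.85 points.
- Share of patients not usually admitted: 100 − 67.4 = 32.6%. The tolerated rise as a share of these: 16.85/32.6 = 51.7%.

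**Size needed for this rule.** The log risk ratio formula gives (1.645 + 0.842)² × 2 × (0.326/0.674) / (ln 1.25)² ≈ 120 per arm; the score method gives 125. The trial plans 3033.

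**Largest observed rise that still passes.** The test passes if ln(p_T/p_C) + 1.645 × SE < ln 1.25, with SE² = (1 − p_T)/(n p_T) + (1 − p_C)/(n p_C). With n = 3033, p_C = 0.674 and p_T = 0.8216, the ratio is 1.219, SE = 0.0152 and the upper bound is 1.2499, which just passes. That is a rise of 14.8 points, or about 448 extra admissions (0.1476 × 3033).

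**Probability of declaring non-inferiority.** This is Φ[(ln 1.25 − ln RR)/SE − 1.645] with n = 3033:

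| True rise | True rate | RR | P(pass) |
|---|---|---|---|
| 5 points | 72.4% | 1.074 | >99.9% |
| 8 points | 75.4% | 1.119 | >99.9% |
| 10 points | 77.4% | 1.148 | 99.99% |
| 12 points | 79.4% | 1.178 | 98% |
| 15 points | 82.4% | 1.223 | 43% |
| 16.85 points | 84.25% | 1.250 | 5% |

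**Can cancelled cultures alone reach the limit?** Let f be the share cancelled and a the usual admission rate among those patients. If every one of them were admitted, the arm's rate would be 0.674 + f(1 − a). With f = 0.30:

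| a (assumed) | Arm rate | P(pass) |
|---|---|---|
| 67.4% | 77.2% | >99.9% |
| 60% | 79.4% | 98% |
| 50% | 82.4% | 43% |
| 43.8% | 84.25% | 5% |
| 40% | 85.4% | 0.5% |

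The value of a at which the limit is reached is 1 − 0.1685/f: 43.8% for f = 0.30, 51.9% for f = 0.35 and 57.9% for f = 0.40. The documents do not give a.

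**Precision on the absolute scale.** SE of the difference = √(2 × 0.674 × 0.326/3033) = 0.0120, or 1.2 points. At equal rates, power is Φ(margin/0.0120 − 1.645): about 80%, 95% and 99% for margins of 3, 4 and 5 points.

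**The case against.** A reader might infer that the admission test is empty: that it cannot fail, because cancelled cultures could hardly push admissions to 84.25% even if every affected patient were admitted. The documents do not support that.

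- The argument needs the admission rate among patients predicted below 5%, which is not given. The 67.4% covers all visits with culture sampling. As the second table shows, the worst case passes almost surely at an average admission rate but fails more often than not once that rate drops below about 51% (1 − 0.148/0.30).
- A true rate of 82.4% lies below the margin, yet the test fails there 57% of the time, because the confidence bound, not the estimate, must clear 1.25.
- The 30% is an approximate validation figure, and the trial excludes several higher-risk groups, so the share cancelled may differ.
- Physicians see the prediction for intervention patients generally, so admissions could also change where the culture is kept.

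All of this stands. It removes the claim that the test cannot fail, but not the point about the margin, which needs no assumption about cancelled cultures.

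Two further objections have some force. The reason for the admission margin may sit in the full protocol or analysis plan, which are not shown; a reason given there would not change how wide the stated margin is. And changing a margin in an open-label trial that has recruited since February 2024, with outcome data extracted automatically to a database managed by the study team, carries a credibility cost. That favours reporting the risk difference with its interval over substituting a new margin without explanation.

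**Conclusion.** The point holds in this form: the 1.25 ratio is too wide for hospital admission to support a useful non-inferiority claim. It tolerates 16.85 points, against 1.9 for mortality, and would pass true rises of up to 12 points with at least 98% probability. This rests on a control rate near 67.4%, 3033 evaluable patients per arm and a large-sample test on the ratio; the score and log risk ratio methods agree closely.

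The test is lax, not vacuous: it can fail under extreme effects. Whether cancelled cultures alone could produce such effects cannot be settled from the documents. The primary outcome and its sample size are not affected. The change should be made because it concerns a key secondary claim, but it does not threaten the trial's main conclusion.

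**What to change.** In the sections Sample size calculation and Statistical analysis, limit the 1.25 ratio so that it no longer governs hospital admission. Base the admission conclusion on the absolute risk difference with its confidence interval. With a standard error of about 1.2 points, a 90% interval is roughly ±2.0 points and a 95% interval ±2.4 points, which is informative.

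If a non-inferiority claim on admission is to be kept, set a separate absolute margin for it, with a stated reason for why that increase is tolerable, before any comparative data are seen. The power figures for 3, 4 and 5 points show only that tighter margins are feasible at the planned size; they do not justify any of those values.

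Cost: an amendment to the text, with no extra patients and no change to the primary analysis. Non-inferiority on admission becomes harder to claim. A margin changed while an open-label trial is running must be documented as such, with its date, its reason and a statement of what data had been seen.

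### The statement that the secondary outcomes needed fewer participants is unsupported for in-hospital mortality and, with the 1.25 ratio margin, very probably wrong

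*Protocol article*

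**What the plan says.** The Sample size calculation section of the protocol article draws its planning figures from 5907 emergency department visits, which "showed a 30-day mortality rate of 7.6%, a hospital admission rate of 67.4% and an average length of stay in the hospital of 6.7 days". It applies a "relative non-inferiority margin of 1.25 for the rates and 1 day for the length of stay", and the sizes are "based on a one-sided alpha of 5% and a target power of at least 80" percent. For 30-day mortality this gives 3033 per arm (6066 in total), raised to 3792 per arm (7584) for 20% dropout. The paragraph ends: "For the secondary outcomes, described in table 2, fewer participants were needed for adequate power".

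Table 2 places in-hospital mortality first among the key secondary outcomes, before admission rate and length of stay. The Statistical analysis section specifies a one-sided non-inferiority test for the ratio of two proportions for the primary outcome, then adds: "Similar tests will be performed for in-hospital mortality rate and the hospital admission rate". The article gives no in-hospital mortality rate, no denominator for it and no separate margin.

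**The concern.** The closing sentence is unqualified, so it covers in-hospital mortality. That outcome appears to have the same kind of test and the same relative margin as the primary outcome, and probably a lower event rate. Under a fixed ratio margin, a lower rate means more participants, not fewer.

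In-hospital mortality is a safety outcome in a trial of withholding a diagnostic test. If the sentence is wrong, readers will take the comparison to have at least 80% power when it may have much less, and will give an inconclusive result more weight than it can bear.

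**Working it through.** **Inputs from the article:** 30-day mortality p = 0.076 in both arms; admission rate 0.674; ratio margin R = 1.25; one-sided alpha 0.05 (z = 1.6449); power 0.80 (z = 0.8416); 1:1 allocation; 3033 evaluable and 3792 enrolled per arm. **Assumed:** in-hospital mortality of 7%, 6%, 5% or 4% of randomised patients, because the article gives no figure.

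**Method.** Farrington-Manning score test for a ratio, true ratio 1:
- Null rates: t1 is the smaller root of 2t² − (R + p + 1 + Rp)t + 2Rp = 0, and t2 = t1/R.
- v0 = t1(1 − t1) + R²·t2(1 − t2); v1 = p(1 − p)(1 + R²).
- n per arm = (1.6449√v0 + 0.8416√v1)² / [(R − 1)p]².
- Power at n = Φ{[√n(R − 1)p − 1.6449√v0] / √v1}.

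**Step 1: reproduce the plan.** At p = 0.076, t1 = 0.08436, t2 = 0.06749, v0 = 0.17558 and v1 = 0.17995. Then n = (0.6892 + 0.3570)² / 0.019² = 3032.2, so 3033 per arm, the stated figure. Power at 3033 is 80.0%. Dropout: 3033/0.8 = 3791.25, so 3792 per arm, also as stated.

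**Step 2: the same test at lower rates.** Worked for 6%: v0 = 0.14101, v1 = 0.14453; n = (0.6177 + 0.3200)² / 0.015² = 3907.2, so 3908. Power at 3033 = Φ[(0.8261 − 0.6177)/0.3802] = Φ(0.548) = 71%.

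| Assumed rate, all randomised | Needed per arm | Power at 3033 | Power at 3792 |
|---|---|---|---|
| 8% | 2869 | 82% | 89% |
| 7.6% | 3033 | 80% | 87% |
| 7% | 3314 | 77% | 84% |
| 6% | 3908 | 71% | 79% |
| 5% | 4739 | 64% | 72% |
| 4% | 5986 | 55% | 63% |

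A simpler log-ratio formula, 2(1 − p)(1.645 + 0.842)² / [p(ln 1.25)²], gives 3891, 4719 and 5960 at 6%, 5% and 4%, within 1% of the table. If all 3792 per arm were evaluable, power would reach 80% from a rate of about 6.2%.

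**Step 3: is the rate likely to be below 7.6%?** Counting index-stay deaths over all randomised patients, in-hospital deaths equal 30-day deaths, minus deaths outside hospital by day 30, plus hospital deaths after day 30. The rate exceeds 7.6% only if the last group outnumbers the middle one. With 100 − 67.4 = 32.6% not admitted and a mean stay of 6.7 days, that is very unlikely.

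**Step 4: admitted patients only.** 3033 × 0.674 gives about 2044 per arm, and the rate among them is the overall rate divided by 0.674.

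| Overall rate | Rate in admitted | Admitted needed per arm | Randomised needed per arm | Power at 2044 |
|---|---|---|---|---|
| 7% | 10.4% | 2153 | 3195 | 78% |
| 6% | 8.9% | 2553 | 3788 | 72% |
| 5% | 7.4% | 3113 | 4619 | 65% |
| 4% | 5.9% | 3953 | 5865 | 56% |

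Power reaches 80% here only if in-hospital deaths are at least about 7.3% of all randomised patients.

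**Step 5: the other key secondary outcomes.** Admission at 67.4% needs 125 per arm, so the sentence is right there. For length of stay with a 1-day margin, it holds if the SD is below √(3033/2)/2.4865 = 15.7 days; the article gives no SD.

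**The case against.** **The decisive rate is missing.** The article gives no in-hospital mortality rate, and the full protocol may. This stands: the 4% to 7% range is an assumption, and the sentence cannot be called proven false. A reader might infer that the in-hospital comparison is known to have less than 80% power, but the documents do not go that far. The point does not rest on an omission, however. It concerns a positive statement that the stated planning figures cannot support.

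**The margin is inferred.** Similar tests describes a type of test, and the 1.25 margin follows a list of rates that does not include in-hospital mortality. The closing sentence may have been meant only for admission rate and length of stay. That is possible, but the sentence points to Table 2 without restriction, and no other margin is given.

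**The denominator is undefined.** Among admitted patients, a rate of 7.6% corresponds to only 0.076 × 0.674 = 5.1% overall. Above that, fewer than 3033 admitted patients per arm are needed, so the sentence could be literally true. Counting deaths in readmissions would also change Step 3. The literal reading does not restore power: about 2044 admitted patients per arm are expected, and power is 72% at 6% overall and 65% at 5%.

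**Dropout may be small.** Mortality is extracted automatically from the record system, so more than 3033 per arm may be evaluable. This softens the power figures, but with all randomised patients as denominator, any rate below 7.6% still needs more participants than the primary outcome. The planned per-protocol analysis makes 3033 a fair base case.

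**Conclusion.** The sentence is correct for admission rate, correct for length of stay unless its SD is very large, and unsupported for in-hospital mortality. For that outcome it is very probably wrong. With a 1.25 ratio margin and all randomised patients as the denominator, it fails at every rate below 7.6%. With admitted patients only, the planned size falls short of 80% power below about 7.3% overall. Over assumed rates of 7% down to 4%, power runs from 77% to 55% at 3033 per arm and from 84% to 63% at 3792.

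The conclusion rests on three things: the 1.25 margin applying to this outcome, a true ratio of 1, and in-hospital mortality lying below 30-day mortality. The first and third are inferences, though well grounded ones.

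A reader might also infer that the trial is too small, or that the in-hospital non-inferiority test should be dropped in favour of estimation. Neither follows. The primary calculation is correct, the primary conclusion is unaffected, and correcting a statement about power does not require a different analysis.

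**What to change.** Do one of the following in the Sample size calculation section:

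- Limit the closing sentence to admission rate and length of stay, after confirming that the observed SD of length of stay bears it out.
- Or state the in-hospital mortality rate in the same 5907 visits, its denominator, the margin that applies and the power this gives at 3033 per arm. If that power is below 80%, say that the in-hospital mortality comparison is not powered to 80%.

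The cost is one sentence, at most one recalculation from data that the sponsor should already hold, and probably a less favourable stated power. Sample size, margin and the pre-specified test can all stay as they are.
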